**Methods:**

A randomised controlled trial with 180 CLBP patients recruited from specialised care will be conducted. Participants will be randomly assigned to three conditions: Control group (CG), CBT, and CBT supported by ICTs (CBT + ICT). Participants belonging to the three conditions will receive a conventional rehabilitation program (back school). The CBT group program will last six sessions. The CBT + ICT group will use the internet and SMS to practice the therapeutic strategies between sessions and in the follow-ups at their homes. Primary outcome variables will be self-reported disability and pain intensity. Assessment will be carried out by blinded assessors in five moments: pre-treatment, post-treatment and 3-, 6-, and 12-month follow-ups. The influence of catastrophizing, fear-avoidance beliefs, anxiety and depression in response to treatment in the primary outcomes will also be analysed.

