Internet-based interventions are very attractive because they address an important issue in the management of chronic diseases: the possibility of systematic training in self-management strategies. Patients learn and practice therapeutic strategies in their natural environment and on their own, promoting self-management and self-efficacy. In fact, a meta-analysis comparing online and traditional interventions reported a higher increase in knowledge and positive behavioural changes in participants with chronic conditions who had participated in an online program [33].

We have developed an internet-based intervention program called TEO (Terapia Emocional Online) that includes two platforms (therapist and patient platform). The system allows the development and management of different therapeutic contents using multimedia elements (therapeutic information and exercises). Patients and therapists can access these contents online. The aim of this application is to practice the therapeutic strategies outside the consultation room as homework and also during the follow-up periods after the treatment programs have finished.

The objective of this study was to design a randomised controlled trial that investigates the short- and long-term efficacy of a CBT program using ICT or not in CLBP treatment. A secondary objective of this trial will be to evaluate the effect of dysfunctional attitudes and beliefs (catastrophizing and fear-avoidance beliefs), depression and anxiety on treatment response. Possible barriers in the implementation of CBT with and without ICT will also be investigated.

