#### Other measures

Demographic information will be collected on the following: age, gender, educational level, current marital status, physical activities (type and frequency) and work (according to the National Economical Activities Classification). Participants will be asked to choose between the following physical activity statuses: sedentary, sedentary with light ambulation, light or vigorous physical activity.

**Clinical data** Weight and height, pain duration (in months), pharmacological treatment history (NSAIDs, analgesics, anxiolytic, skeletal muscle relaxants and corticosteroids (specifying type, duration and dosage)), physical therapy (type and duration), imaging and other radiological tests, neurophysiological tests, as well as work status will all be recorded. These data will be gathered by interviews and from the participants’ clinical history.

Comorbidity will also be considered. Different factors like hypertension, arthrosis, diabetes, heart disease, chronic obstructive pulmonary disease (COPD) or smoking can affect the course of low back pain and its disability. Comorbidity will be assessed with the Charlson comorbidity index (CCI) [49]. The CCI evaluates 13 different comorbid conditions. Each condition is assigned a score depending on the risk of dying associated with each one. Scores are added to provide a total score to predict mortality. Psychiatric comorbidity will be evaluated with the Brief Symptom Inventory (BSI) [50] adapted by Ruipérez et al. [51].

Finally, all the different interventions that patients could receive besides the treatments offered in this study will be recorded using the interview with the patient and the clinical history as sources. Pharmacological treatment, physical therapy (in public or private services) and infiltrations will also be recorded.

**Satisfaction with the treatment** The Spanish adaptation of the Borkovec and Nau questionnaire [52] will be used. Participants have to respond using an 11-point scale (0 to 10) to give their opinion on the treatment received (for example, how logical the treatment was for them; if they are satisfied; if the treatment was useful; and if they would recommend the treatment to other people). Clinicians will also answer an adapted version of the questionnaire regarding satisfaction with the treatment program.

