Intra-group changes in the continuous variables along the time points will be explored with Student’s T-test for paired samples. To assess if there are differences among the groups according to pain, disability and the rest of the variables, we will use analysis of covariance (ANCOVA) for each dependent variable. In all the tests, the independent variable will be the group, while the covariate variable will be the basal level of each dependent variable. It will be necessary to have comparable levels of both types of variables to understand correctly the ANCOVA results. Therefore, we will perform different Student’s T test estimations, one for each dependent variable, considering each group as an independent variable in each case. To evaluate whether the changes in the three groups have happened in a different way, we will estimate different ANOVA, an analysis for each dependent variable. In all cases, the independent variable will be the group and time in which the data are collected. In this analysis, we will also study possible interactions. Furthermore, we will evaluate the correlations between the variables using Rho-Pearson and Spearman according to normality. We will also use two multiple linear regression models for pain and disability as dependent variables and in both models, gender, age, pain, catastrophizing, fear avoidance, days taken off at work and time evolution will be employed as independent variables.

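### No specified model can show how catastrophizing, fear-avoidance, anxiety or depression change response to treatment, because none combines treatment arm with any of these factors as a moderator

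*Protocol article*

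**What the plan says.** The objective appears in three places in the protocol article.

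- The Background says that the trial will "evaluate the effect of dysfunctional attitudes and beliefs (catastrophizing and fear-avoidance beliefs), depression and anxiety on treatment response".
- The Abstract (Methods) ties the same four factors to the primary outcomes: "The influence of catastrophizing, fear-avoidance beliefs, anxiety and depression in response to treatment in the primary outcomes will also be analysed".
- The Sample size section plans a further analysis of response by high or low level of each of the four factors, on the Roland-Morris score, with its own alpha (0.05), power (0.8, printed as beta) and number (28 per group). It names no test or model.

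The models are under Collection and data analysis.

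- ANCOVA, one per dependent variable: "the independent variable will be the group, while the covariate variable will be the basal level of each dependent variable".
- ANOVA, one per dependent variable: "the independent variable will be the group and time in which the data are collected. In this analysis, we will also study possible interactions".
- Regression: "two multiple linear regression models for pain and disability as dependent variables", with one predictor list for both: "in both models, gender, age, pain, catastrophizing, fear avoidance, days taken off at work and time evolution will be employed as independent variables".

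The section also announces pairwise correlations between variables.

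**The concern.** To say that a factor affects response to treatment is to say that the difference between arms depends on that factor. Estimating this requires the arm, the factor and their product in one model. The regressions hold two of the four factors and no arm; the ANCOVA and ANOVA hold the arm and none of the factors as moderators.

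If the section is followed as printed, the coefficients for catastrophizing and fear avoidance describe who has more pain or disability whatever the treatment. The risk is that these prognostic coefficients are reported as predictors of response to CBT or CBT + ICT. Anxiety and depression would have no coefficient in any model specified there.

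A smaller problem lies in the same list. Pain is a predictor in both models, including the one in which pain is the outcome, and the text does not say that the baseline value is meant. The psychological scores have the same gap. They are also secondary outcomes measured after treatment, and a post-treatment value could itself be changed by the arm.

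**Working it through.** **1. Content of each model against the objective.**

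| Analysis | Arm | Catastrophizing | Fear avoidance | Anxiety | Depression | Arm x factor |
|---|---|---|---|---|---|---|
| ANCOVA | yes | no | no | no | no | no |
| ANOVA | yes | no | no | no | no | no (arm x time only) |
| Two regressions | no | yes | yes | no | no | no |

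The table shows the factors in the role of moderators of pain and disability. Where a psychological score is itself the outcome of an ANCOVA, its baseline enters as a covariate, but that says nothing about response in pain or disability. The correlations involve no arm. No row has both an arm and a factor.

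**2. What a regression without arm estimates.** With equal arms and a factor balanced by randomisation, the pooled slope is about the mean of the three arm-specific slopes. Two invented cases show that this mean carries no information on effect modification:

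- Slopes +1 (control), -0.5 and -0.5 (active arms): pooled slope = (1 - 0.5 - 0.5)/3 = 0, although the interaction is -0.5 - 1 = -1.5.
- Slopes +1, +1 and +1: pooled slope = 3/3 = 1, although the interaction is 0.

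These slopes are illustrations and do not come from the protocol. The first set was chosen to cancel.

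**3. The plan's figure of 28 per group.** Inputs from Sample size: difference 3 points, SD 4, two-sided alpha 0.05, power 0.80. The normal approximation for two means gives

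n = 2 x (1.960 + 0.842)² x 4² / 3² = 2 x 7.85 x 1.778 = 27.9, rounded up to 28.

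The stated figure reproduces. It is the number for one difference between two groups.

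**4. The same inputs for an interaction.** An interaction is a difference of two differences. With the two arms compared each split into high and low, SE = SD x √(2/n_high + 2/n_low). Assumptions that are not in the protocol: median split, an interaction of 3 points, one pairwise arm comparison.

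- 60 per arm (30 high, 30 low): SE = 4 x √(4/30) = 1.461; 3/1.461 - 1.960 = 0.094; power about 54%.
- 51 per arm after 15% attrition (25.5 each): SE = 4 x √(4/25.5) = 1.584; 3/1.584 - 1.960 = -0.066; power about 47%.
- With a 30/70 split, the corresponding powers are 47% and 41%.
- For an interaction of 1.5 points, power is 14 to 18% across these settings.
- For 80% power at 3 points: n per cell = 4 x (4 x 2.802/3)² = 55.8, so 56 per cell, or 112 per arm. This is twice the stated 28 per cell.

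**The case against.** The strongest reply is that the regressions were never meant to answer the response objective. The section introduces them after the correlations and does not mention treatment response, and their predictors read like an ordinary prognostic model. This stands: the link between the regressions and the objective is an inference. It does not close the gap. If the regressions are not the response analysis, then no model in the section is.

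A reader might infer that anxiety and depression will never be analysed. The protocol does not support that, because the Sample size section plans a high/low analysis that names both. What can be said is that both are absent from every specified model. One can add that an article may leave the test for that high/low analysis to a fuller document. That is fair, and the missing test is not the complaint. The complaint is that the model content that is printed does not match the stated objective, and that 28 per group does not size an interaction.

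A reader might infer that pain is being used to predict itself. Baseline pain would be a normal covariate, and the ANCOVA in the same section adjusts for the baseline outcome. The wording is ambiguous; circularity is not shown.

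A reader might also infer that days off work is a predictor nobody collects, since Other measures says "neurophysiological tests, as well as work status will all be recorded". A summary list drawn from interviews and clinical history does not show that the item is uncollected, so nothing is claimed on it.

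**Conclusion.** The point holds as a mismatch between a declared, separately sized secondary objective and the models printed for the trial. None of the specified models can estimate how any of the four factors modifies the effect of CBT or CBT + ICT, and two of the four enter none of them. This follows from the model content alone and does not depend on the illustrative slopes.

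The power figures (about 47 to 54% for a 3-point RMDQ interaction) rest on a median split, SD 4, two-sided alpha 0.05 and one pairwise comparison. They show that a corrected analysis would be exploratory.

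It would be too strong to treat this as a threat to the trial's main result. The primary comparison (intention to treat, 12 months, ANCOVA with arm and baseline) is untouched. The change is worth making but is not essential to the primary conclusion.

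**What to change.** - **Specify a model for the response objective.** Fit the 12-month ANCOVA for RMDQ and for the pain NRS (stating which of the two pain scales) with arm, baseline outcome, baseline moderator and arm x moderator. Do this in turn for PCS, FABQ, HADS-anxiety and HADS-depression, preferably as continuous scores.
- **Reconcile it with Sample size.** Either replace the high/low plan or keep it as a descriptive display. State that 28 per group refers to a simple two-group difference and does not size an interaction test.
- **If the two regressions are kept,** add arm, state that pain and the psychological scores are baseline values, and describe the models as prognostic.
- **Label the response analysis exploratory and acknowledge multiplicity.** There are at least 2 outcomes x 4 moderators = 8 models, each with more than one arm contrast.

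The cost is a change of wording before analysis. All four scales are already collected, so no new data are needed. The drawback is low power: intervals for the interactions will be wide, and a non-significant result should not be read as absence of moderation.

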### Privacy and data protection

Personal passwords and data encryption as Advanced Encryption Standard (AES) will be used. The project will comply with current guidelines in Spain and EU for patient protection in clinical trials according to collection, storage and the keeping of personal data.

### Ethical issues

The trial will comply with Helsinki’s Declaration. This project has been approved by the ethics research committee of Hospital Arnau de Vilanova in Valencia. As for the intervention and assessment protocols used in this study, there is nothing that poses a risk to the participants, according to existing knowledge. The treatment protocols to be developed are based on CBT, which is first and foremost a learning- or teaching-based therapy. Thus, the treatment is not invasive at a cognitive level, except as far as any learning or teaching is concerned.

## Discussion

There is no gold standard therapy for chronic low back pain. Thus, it is necessary to find new treatment strategies that improve on current results. In this work, we propose to apply a randomized controlled clinical trial to test the effectiveness of a CBT intervention using ICT or not for treating CLBP. The ICT will use the online program TEO and mobile phone SMS. TEO is a completely open system that allows therapists to create and show personalized therapeutic material to patients online. The primary data concerning TEO system’s acceptance by patients has already been obtained [55].

Internet use in the Spanish population is high and to rise, with Spain taking the 7th position in Europe with regard to Internet use. In 2012, two out of three homes had broadband connection, 8.0% more than in 2011 [56]. Therefore, the internet is a promising way of delivering information and interacting with patients. If the therapy designed in this project is effective, it could be applied in daily clinical practice to improve CLBP treatment.

Moreover, this trial opens the door to new research that could explore the possibility of using certain therapies, or some of them, in the patient’s own home. In this way, the healthcare burden of treating CLBP at a clinical setting could be reduced. Moreover, treatment adherence can be improved.

These results will support and contribute to the literature, indicating the great potential for technological adjuncts like the ones designed in the present study. Engagement during and between therapy sessions could be enhanced by employing electronic homework and aftercare practices to increase adherence and patient satisfaction [57].

If the results of this study are positive, there will be a manualized CBT program that could be used easily in the daily care of CLBP patients and applied in two versions: traditional (for those patients without internet access) and with the support of internet and SMS. It will be possible to train therapists easily on administering this program, not requiring specialised training. This treatment program will contribute to improving the resources included in the clinical guidelines for CLBP treatment.

This study has some limitations. Although the randomized sequence will be hidden, due to the nature of the treatments, it will not be possible to blind the participants to the group that has been assigned to them. It is possible that patients in the CBT groups will feel more looked after, therefore giving more pleasing answers. Despite not being a blinded placebo, the control group will also attend the back school group sessions to try to minimize this effect. We have assumed that patients in the three groups will have the same treatment apart from the interventions included in the study. During the trial, it may be possible that the blinding of the clinicians and physiotherapists is lost, leading to possible selective co-interventions. Patients will be asked not to tell their clinicians, physiotherapists or orthopaedic surgeons their treatment group. Their clinical history will only note that the patient attends educational sessions for CLBP.

Most of the clinical trials that have studied CBT modalities in other countries have been performed with patients in primary care. This project will be carried out in specialized care in the Spanish healthcare system, which reaches all the population and whose access is controlled by primary care. The results of clinical trials on CBT tend to be much better in specialized care than primary one, possibly because of a selection bias that causes the patients in specialized care to be usually in a worse condition [58]. Patients will continue to be treated by their primary care doctors to whom they have free access. The recommendations that doctors may give can vary due to their own beliefs and attitudes about back pain, regardless of their knowledge about guidelines [59].

We hope this work will offer useful data about the short- and long-term efficacy of a treatment of disability and pain. This could open new avenues for developing public health strategies and treatments, leading to a better care of the patients suffering from this problem.
